### Statistical analysis

All analyses will be done on the intention-to-treat group of participants who have been randomized regardless of whether they receive any treatment. Missing data will be replaced according to the principle of the last observation carried forward. A variance analysis reject the global hypothesis H_0_: "There is no difference in the success probability between two groups." The significant level used for the statistical analysis is 5%, therefore P < 0.05 indicates significance. Analysis of variance (ANOVA) for repeated measures is used to compare the two groups. Comparisons within groups for the outcomes in each one of the time point were done using the Tukey's post hoc test of Multivariate Analysis of Variance (MANOVA). In the case of proportions, a *chi-square test *is applied. Stratified analysis within five different centers will be performed to control confounding factor if necessary. All analyses are performed using the Statistical Package for the Social Sciences (SPSS) software program (version 13.0) for Windows XP.

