### Participants

One hundred and forty patients with migraine without aura enrolled in the trial are recruited from outpatient in acupuncture clinics of the five hospitals. The main inclusion criteria are: patients suffering from migraine without aura (more than 2 migraine attacks in 4 weeks), diagnosed according to diagnostic criteria of the International Headache Society [1]; male or female; aged 18–65 years; patients who had not used acupuncture or drugs with migraine prophylactic effects within the last 3 months; patients who have given written informed consent.

The main exclusion criteria are: tension-type headache, cluster headache and other primary headaches; secondary headache and other neurological diseases; neuralgia of the face or head; pregnancy, nursing mother or insufficient contraception; use of prophylactic migraine medication in the last 3 months; therapy with β-blocker in the last 3 months; intake of antipsychotic or antidepressant drugs; participation in another clinical trial; having family history of depression, Parkinson disease and other extra-pyramidal diseases.

According to the previous studies in China and our pilot study, we anticipate that the proportion of responders [13] (50% or greater reduction in attack frequency) would be 65% [14,15] in control group and 90% [16] in acupuncture group. Based on 0.9 power to detect a significant difference (α = 0.05, two-sided), 56 patients are required for each group calculated by EpiCalc 2000 Version 1.02. To compensate for dropout patients, we plan to enroll 70 patients per group.

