### Outcome measures

The efficacy of acupuncture for migraine prophylaxis is assessed by the following primary outcome measures:

1. Change in frequency and duration of migraine attacks [13].

2. The proportion of responders, defined as the proportion of patients with a reduction of migraine days by at least 50% [13].

3. Visual Analogue Scale (VAS) to assess the severity of migraine pain [17].

4. Short-Form of McGill Pain Questionnaire (SF-MPQ) [17,18].

The secondary outcome measures include:

1. The summary scales of the SF-36 [19,20].

2. Intake of acute-medication [13].

3. Number of patients with adverse side effects [21].

4. Change in the frequency of nausea and vomiting [22].

The outcome measures above will be assessed before the treatment, the week of the last acupuncture session and 12 weeks after the last acupuncture session.

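### The rule that every analysis uses all randomised patients, treated or not, also covers adverse side effects, so any never-exposed patient lowers an arm's side-effect rate slightly

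*Protocol article*

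**What the plan says.** The Statistical analysis section sets one population for everything: "All analyses will be done on the intention-to-treat group of participants who have been randomized regardless of whether they receive any treatment". The next sentence sets one missing-data rule, also without exception: "Missing data will be replaced according to the principle of the last observation carried forward". Later in the section a chi-square test is assigned with the words "In the case of proportions".

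The Outcome measures section lists as the third secondary outcome "Number of patients with adverse side effects", and closes its list with: "The outcome measures above will be assessed before the treatment, the week of the last acupuncture session and 12 weeks after the last acupuncture session". That sentence makes no exception for side effects either.

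Under Methods, the allocation envelope is opened once the baseline period is over and the patient is registered, which is before treatment starts. The Participants section gives the arm size: "To compensate for dropout patients, we plan to enroll 70 patients per group". The article names no separate population for side effects.

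**The concern.** Analysing everyone as randomised is right for efficacy, because it preserves the randomised comparison. For side effects the question is what happens to people who are needled or take the capsules. A patient who received neither adds nothing to the numerator but adds one to the denominator.

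The missing-data rule works in the same direction. A never-treated patient without follow-up has only the pre-treatment assessment, so carrying the last observation forward records that patient as free of side effects. Read literally, the rule would do the same to a treated patient who leaves before the assessment in the week of the last session, unless side effects are also recorded as they occur.

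What is at stake is the accuracy of the tolerability figures. The Background section gives the side effects of prophylactic drugs as a reason that limits their use, so readers will look at these rates.

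**Working it through.** **The plan's own figure.** The arm size is the denominator at issue, so it is checked first. The Participants section states "Based on 0.9 power to detect a significant difference (α = 0.05, two-sided), 56 patients are required for each group", for responder proportions that "would be 65% [14,15] in control group and 90% [16] in acupuncture group". With pooled variance under the null and no continuity correction:

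- mean proportion = (0.65 + 0.90)/2 = 0.775
- null term: 1.960 × √(2 × 0.775 × 0.225) = 1.960 × 0.5906 = 1.157
- alternative term: 1.282 × √(0.65 × 0.35 + 0.90 × 0.10) = 1.282 × 0.5635 = 0.722
- n = (1.157 + 0.722)² / 0.25² = 56.5, rounded up to 57

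The stated 56 is one patient lower and gives power 0.897, so it reproduces. Enrolling 70 allows for 1 − 56/70 = 20% dropout, or 14 patients per arm. None of this is affected by the present point.

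**Inputs for the side-effect rate.**

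- Denominator under the plan: 70 per arm (Participants and Statistical analysis sections).
- u, the number in an arm who never receive a session or a dose: not in the article, so assumed.
- p, the side-effect rate among exposed patients: not in the article, so assumed.

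**Formula.** The expected number of affected patients is p × (70 − u). Divided by all 70 randomised, the reported rate is p × (70 − u)/70.

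| u in the arm | Factor (70 − u)/70 | Assumed p = 10% | Assumed p = 20% | Assumed p = 30% |
|---|---|---|---|---|
| 1 | 0.986 | 9.9% | 19.7% | 29.6% |
| 3 | 0.957 | 9.6% | 19.1% | 28.7% |
| 7 | 0.900 | 9.0% | 18.0% | 27.0% |
| 14 | 0.800 | 8.0% | 16.0% | 24.0% |

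Each never-treated patient costs 1/70 = 1.4% in relative terms. The last row is an extreme bound: it takes the whole dropout allowance as patients who never started, whereas many dropouts would have had some treatment.

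**Comparison between arms.** If u is the same in both arms, both rates shrink by the same factor. Their ratio is unchanged, and the absolute difference shrinks by (70 − u)/70. Power hardly moves: for assumed true rates of 10% and 20% with u = 7 in each arm, it is 0.343 on all 70 randomised and 0.348 on the 63 exposed.

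Only unequal non-starting distorts the comparison. With 0 never treated in one arm and 7 in the other, an equal true rate of 20% would appear as 20% and 18%. This is an illustration; the article contains nothing that predicts it.

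**The case against.** The strongest reply is that this reads one general word too literally. The section is a single paragraph of a journal article, the sentence is a standard intention-to-treat declaration, and the hypothesis named in that paragraph concerns success, which is efficacy. A safety population is commonly defined in a full protocol or analysis plan, and its absence here would be no finding. This has some force, but the article is not silent. It fixes a population for every analysis and expressly brings in untreated patients, so an analysis plan with a different population for side effects would contradict it.

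A second reply is that the outcome is a count, which untreated patients do not alter. That is correct, and it limits the point to rates and to any chi-square comparison of them.

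A reader might also infer three stronger things that the article does not support:

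- **That the comparison is biased towards one arm.** This needs non-starting to differ by arm. Patients are blinded, and both arms receive needling three times a week and a nightly capsule of identical appearance. A patient who withdraws before the first session or dose would have little arm-specific reason to do so.
- **That rates are understated in both arms.** This holds only if both arms have non-starters. The effect is arm by arm.
- **That patients are counted in the wrong arm.** Nothing in the article suggests that anyone receives the other arm's treatment.

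**Conclusion.** The point holds in a limited form. As written, the population rule covers side effects, and any never-exposed patient lowers the reported rate in that patient's arm by a known factor. The direction is certain. The size is small, at about 1.4% relative per patient, and rests on a number of non-starters and a side-effect rate that the article does not give. If every randomised patient starts treatment, the population rule changes nothing.

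Bias between arms remains a hypothetical possibility in this design. The primary outcomes, the sample size and the efficacy conclusion are untouched. This is a minor wording correction, worth making because it is easy.

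**What to change.** Limit both the intention-to-treat sentence and the last-observation-carried-forward sentence to efficacy outcomes. Then add a sentence such as: adverse side effects will be analysed, without carrying observations forward, in all randomised patients who received at least one needling session or at least one dose of study medicine or placebo; the number per arm who received neither will be reported. The article gives no reason to regroup patients by treatment received, so the change need go no further.

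The cost is a few lines of text and a record of who started treatment. The downside is that the side-effect comparison leaves out randomised patients who never started and so no longer covers everyone randomised. Reporting their number in each arm lets a reader see how much that matters, and recover the rate over all 70 if wanted.

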### Procedures

According to predetermined randomization envelopes, 140 eligible patients are randomly allocated to acupuncture group or control group (see Figure 1). The patients have an equal probability of being assigned to either of two groups. Patients need to record headaches and usage of acute medication in headache diary from baseline period to the 16^th ^week after randomization. According to Case Report Form including all outcome measures, endpoints are collected separately 16 weeks after randomization by blinded telephone interviewers in the five hospitals to evaluate the long term effect of acupuncture prophylaxis.

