### Intervention

In addition to rigorous methodological quality, both verum acupuncture and sham acupuncture interventions have been proposed based on a broad literature review and a consensus with acupuncture experts in Beijing Traditional Chinese Medicine Hospital. We conducted a pilot study with sample size 32 per group to confirm the efficacy of verum acupuncture compared with sham acupuncture. Besides, the interventions of two groups are based on the experiences of physicians who had worked with acupuncture for 20 years.

In the acupuncture group, 3 acupuncture sessions per week are carried out and placebo medicine is taken once a night for 4 weeks. In the control group, medicine (flunarizine) once a night for 4 weeks is given and 3 sham-acupuncture sessions are given per week. There are several common approaches of verum/sham acupuncture in both groups including: bilateral points; usage of disposable, sterile steel needles (0.32 mm × 40 mm); 10–12 needles used each time; skin disinfection with 75% alcohol; needles retention for 30 minutes and no moxibustion or electrical stimulation. Patients of both groups received 12 sessions of verum/sham acupuncture in 4 weeks.

The placebo medicines have exactly the same appearance as true medicines (flunarizine). Both Flunarizine and placebo are taken 10 mg once per night for the first 2 weeks and then 5 mg once per night for the next 2 weeks. All patients are allowed to treat acute headaches as need, but the type and dose of acute medications should be recorded in a headache diary.

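### Carrying the last observation forward lets end-of-treatment values stand in for missing week-16 values, and so is liable to bias the long-term comparison

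*Protocol article*

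**What the plan says.** The Statistical analysis section gives a single rule for incomplete data: "Missing data will be replaced according to the principle of the last observation carried forward". It exempts no outcome, visit or reason for missingness. The sentence before it sets the population: "All analyses will be done on the intention-to-treat group of participants who have been randomized regardless of whether they receive any treatment". Groups are then compared by repeated-measures ANOVA, and proportions by a chi-square test.

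The Outcome measures section fixes three time points for every primary and secondary outcome: "The outcome measures above will be assessed before the treatment, the week of the last acupuncture session and 12 weeks after the last acupuncture session". The Intervention section gives the length of treatment: "Patients of both groups received 12 sessions of verum/sham acupuncture in 4 weeks". The three assessments therefore fall at baseline, about week 4 (end of treatment) and about week 16 (12 weeks off treatment). The Procedures section says that the week-16 data are collected "to evaluate the long term effect of acupuncture prophylaxis".

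Two other statements bear on the point. Procedures describes a diary: "Patients need to record headaches and usage of acute medication in headache diary from baseline period", kept up to week 16. And the secondary outcomes on the same three-visit schedule include "Number of patients with adverse side effects".

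**The concern.** With three assessments, the rule does one of two things to a patient with no week-16 value.

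- If the patient was seen at week 4, the end-of-treatment value is entered as the value 12 weeks after treatment stopped. That presupposes that the effect lasts, which is the question the week-16 assessment is there to answer.
- If the patient left before week 4, the baseline value is entered. For the responder outcome this means a non-responder.

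So one rule makes opposite assumptions, full persistence or no effect at all, depending only on when the patient left. A difference between groups at week 4 can pass into the week-16 result through patients who were not observed then. At stake is the long-term comparison of acupuncture with flunarizine. The week-4 comparison is not affected in this way.

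**Working it through.** **Inputs from the article (Participants).** The responder rates assumed for the sample size "would be 65% [14,15] in control group and 90% [16] in acupuncture group"; two-sided α = 0.05; power 0.9; 56 required and 70 enrolled per group.

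**The plan's own figures.** For 65% v 90%, the pooled-variance formula without continuity correction gives 57 per group, against 56 stated. Power at 56 is 0.897. The enrolment margin is 1 − 56/70 = 0.20, so 70 per group implies a 20% allowance for dropout, although no rate is stated. The sample size is not in question here.

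**Assumptions, not in the article.** The 90% and 65% are taken as week-4 rates (the article does not tie them to a visit). True week-16 rates are taken as equal. Loss is unrelated to outcome. Anyone missing at week 16 has no later diary data in use. Rejection rates are exact probabilities for the uncorrected chi-square test with 70 per arm, treating each arm as binomial at the rate shown.

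**Formula.** Let m₁ be the fraction lost after week 4, m₀ the fraction lost before week 4, p₄ the week-4 rate and p₁₆ the true week-16 rate. The rate under the rule is

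(1 − m₁ − m₀)·p₁₆ + m₁·p₄ + m₀·0.

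**Main example: m₁ = 0.20, m₀ = 0, p₁₆ = 0.50 in both arms**

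- Acupuncture: 0.80 × 0.50 + 0.20 × 0.90 = 0.58
- Control: 0.80 × 0.50 + 0.20 × 0.65 = 0.53
- False difference: 5 points. Rejection is 9.2%, against 5.2% when both arms are at 50%. If exactly 14 patients per arm are carried forward, it is 8.4%.

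**Half the loss before week 4: m₁ = m₀ = 0.10**

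- Acupuncture: 0.80 × 0.50 + 0.10 × 0.90 = 0.49
- Control: 0.80 × 0.50 + 0.10 × 0.65 = 0.465
- False difference: 2.5 points. Rejection is 6.2%.

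**Other settings, all loss after week 4**

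| True week-16 rate, both arms | Lost: control / acupuncture | Control | Acupuncture | False difference | Rejection |
|---|---|---|---|---|---|
| 50% | 10% / 10% | 51.5% | 54.0% | +2.5 points | 6.1% |
| 65% | 20% / 20% | 65.0% | 70.0% | +5.0 points | 9.8% |
| 65% | 10% / 30% | 65.0% | 72.5% | +7.5 points | 16% |
| 50% | 10% / 30% | 51.5% | 62.0% | +10.5 points | 24% |
| 50% | 20% / 0% | 53.0% | 50.0% | −3.0 points | 6.6% |

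**No waning.** If week-16 rates equal week-4 rates (90% and 65%) and loss is after week 4, the carried value has the right expectation: 0.80 × 0.90 + 0.20 × 0.90 = 0.90, and likewise 0.65. The bias is zero.

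**The case against.** **The harm depends on facts that the article does not give.** The main example needs all 20% of the loss to come after week 4 and a 25-point effect to vanish completely. With mixed timing of loss or only 10% loss, rejection is about 6%; with persistence there is no bias; and the sign can reverse. This stands. It limits the conclusion to liable to bias and argues against the highest severity. It does not rescue the rule, which is safe only if the effect persists or few patients are lost.

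**Diaries run to week 16.** For headache and acute-medication outcomes the last observation may fall well after week 4. This also stands. It weakens the point for attack frequency and responders, on which the arithmetic is based. VAS, SF-MPQ and SF-36 are not described as diary items, so for them the last observation before week 16 is the week-4 assessment.

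**Four stronger readings are tempting, and the article does not support them.**

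- A reader might infer that analysing 70 values when 56 were observed understates the standard error, by a factor of √(56/70) = 0.894. In the chi-square setting it does not. The 14 carried values are real week-4 observations from 14 other patients. In the main example the SD of the acupuncture proportion is √(56 × 0.50 × 0.50 + 14 × 0.90 × 0.10)/70 = 0.056, while the usual formula gives √(0.58 × 0.42/70) = 0.059. The fault is bias.
- A reader might infer that the rule hides adverse effects that cause dropout. The Statistical analysis section does not mention adverse effects, and an event recorded before dropout counts whatever the rule says. Only unrecorded events would be lost. That is a matter of data collection, which a condensed article may leave to the full protocol.
- A reader might infer that attack-free patients have an earlier pain score carried forward. Nothing says that attack-free periods are coded as missing.
- A reader might infer that counting missing patients as non-responders would be safe. With true rates of 50% in both arms and 10% control / 30% acupuncture missing, it gives 0.90 × 0.50 = 45% v 0.70 × 0.50 = 35%, a false 10-point difference with 22% rejection. Carrying forward gives 10.5 points and 24% there.

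**Conclusion.** The concern holds for the week-16 comparison. The article fixes a rule under which end-of-treatment values can represent patients 12 weeks off treatment, at the visit meant to show whether the effect lasts. Over the settings examined with equal true rates, the false difference runs from −3.0 to +10.5 points. It is 5 points with about 9% rejection in the main example, and zero under persistence. Those figures rest on assumed dropout, its timing and the amount of waning; only the 90%, the 65% and the 20% enrolment margin come from the article. The mechanism applies most clearly to VAS, SF-MPQ and SF-36. Severity: should be fixed.

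**What to change.** - **Continuous outcomes.** Replace last observation carried forward and repeated-measures ANOVA by a likelihood-based mixed model on the observed visits (SPSS MIXED), without single imputation.
- **Responders.** Use the available diary data up to week 16 and do not carry week-4 status forward. Report both multiple imputation and missing-as-non-responder, since neither is safe alone under unequal dropout.
- **Adverse effects.** State that the count is of treated patients with any event recorded after the first treatment, without carrying forward. This clarifies the analysis and needs no new data collection.

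The cost is revised analysis wording, a little programming in the same package and slightly wider intervals. The change should be made before unblinding, so that it cannot look driven by the data.

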## Discussion

The question we put forward in this clinical trial is: "Is acupuncture prophylaxis as effective as flunarizine for migraine?" Flunarizine is a drug classified as a calcium channel blocker, which is commonly used in China for migraine prophylaxis. A large sample size study considered that flunarizine is safe and effective for the prophylactic treatment of migraine in China [23]. Therefore, we compare the efficacy of acupuncture with flunarizine which is chosen as a standard drug therapy. The strength of our trial is strictly concealed randomization, the successful blinding of the patients, data collection in diaries. Moreover, in this trial all physicians applying acupuncture treatments have more than 20 years of clinical experience of acupuncture.

According to the theory of traditional Chinese medicine, migraine headaches can be considered as syndromes of meridians [24]. So the acupuncture intervention is given based on the concept of syndrome differentiation of meridians. As an important part of the theory of meridians, syndrome differentiation of meridians has been performed in clinical practice for thousands of years. The aim of syndrome differentiation of meridians is to analyze the involvement of the meridians according to the distribution and indication of meridians for the purpose of providing evidence for selecting the needling methods [25]. For example, most migraine patients with headache on the temporal side, where the distribution of meridians of foot-Shaoyang, should pertain to Shaoyang headache, while some migraine patients with headache on the forehead should pertain to Yangming headache, because forehead is the distribution of meridians of foot-Yangming. In the case of Shaoyang headache, SJ5 and GB34 can be added besides obligatory points that have to be needled in the trial.

The protocol of sham points is developed in our trial according to international considerations about the methodological problems of sham acupuncture [26]. To avoid any effects on headache, firstly we searched points without effect on headache from both ancient and modern literature. This method of selecting sham points can be seen in Alecrim (2008) [22], but our research must be more extensive, because we searched many Chinese articles, particularly ancient books, which have not yet been translated into English. Secondly, as Linde (2005) [27] did, distant non-meridian point is used as sham point by needling 3 mm apart from the points without effect on headache to further avoid the meridian affects in the control group. Last but not least, there are 30 points without effects on headache extracted, but only 5 points will be used to each patient in control group. Points, which are chosen and made up as a control subgroup, are determined by computer-made randomization. This process of confirming sham points could further eliminate potential effects on headache.

To mask the patients in our trial, sham acupuncture is adopted in the control group while placebo medicine is used in acupuncture group, which is considered to benefit the homogeneity of potential psychological effects and improve compliance of patients in China. Alecrim (2008) [22], Diener (2006) [13] and Linde (2005) [27] reported that sham acupuncture had similar effects to verum acupuncture in reducing migraine headaches and both interventions were effective. They thought that several nonspecific factors could explain the high improvement of the sham group, such as the patient's belief in positive results of the acupuncture treatment and the frequent patient's contact with the acupuncturist. Even though in our trial these factors have been standardized as strictly as possible and the selection of sham points is different from previously published trials, we cannot rule out that sham acupuncture intervention may have some physiological effects. The nonspecific physiological effects of needling may include local alteration in circulation and immune function as well as neurophysiological and neurochemical responses as reported [28,29]. Moreover, the placebo effects may be higher in pain sufferers than in patients suffering from other complaints [30] and invasive technical proceedings may have higher analgesic effects than oral drugs [31,32]. Our design therefore might prefer the flunarizine group.

Acupuncture has been used for alleviating acute/chronic pain for thousands of years. The efficacy of acupuncture as abortive therapy for patients with migraine headaches has been proved by many studies [12]. Some studies suggested that sumatriptan was more effective than acupuncture at relieving headache [33]. Therefore, the purpose of this trial is not to discuss the efficacy of acupuncture as painkiller but evaluate the efficacy on preventing migraine attack. The results of our trial will be helpful to supply the evidence on the efficacy of acupuncture for migraine prophylaxis in China.

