Many studies have already reported encouraging results in the therapy of migraine by acupuncture. In 2001 a systematic review on acupuncture for idiopathic headache had underlined the existing evidence that acupuncture had an effective role in the treatment of patients with migraine [12], but methodological or reporting shortcomings were found in the majority of the studies, so the evidence was insufficient to determine the efficacy of acupuncture compared to medication, or to wait list control or sham acupuncture, in the management of patients with migraine. Since that systematic review, several large, randomized trials on the effectiveness of acupuncture as treatment for migraine prophylaxis have been published in western countries, but there seems to be a lack of high quality randomized controlled trials from China. China is the origin of acupuncture and the country where acupuncture has been used most commonly in clinical practice. Therefore, we are performing a randomized controlled trial to investigate the efficacy of acupuncture compared with flunarizine in patients who have frequent migraine attacks in China.

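### The Discussion asks whether acupuncture matches flunarizine, but the plan tests for a difference with no margin, so a non-significant result could be misread as equal efficacy

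*Protocol article*

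**What the plan says.** The Discussion of the protocol article introduces the following as the question the trial puts forward: "Is acupuncture prophylaxis as effective as flunarizine for migraine". The other statements of aim are neutral. The Background says the trial is "to investigate the efficacy of acupuncture compared with flunarizine in patients who have frequent migraine attacks in China", and the Abstract is worded in much the same way.

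The operative sections describe a test of difference:

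- **Participants (sample size):** the responder proportions "would be 65% [14,15] in control group and 90% [16] in acupuncture group", with the size set as "Based on 0.9 power to detect a significant difference (α = 0.05, two-sided"). This gives 56 per group, raised to 70 for dropout.
- **Statistical analysis:** the null hypothesis is "There is no difference in the success probability between two groups". For the test, "In the case of proportions, a *chi-square test *is applied", and for the decision rule, "therefore P < 0.05 indicates significance".

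The article gives no equivalence or non-inferiority margin and no criterion based on a confidence interval. It does not say how a non-significant result would be interpreted.

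**The concern.** A question about matching an active standard drug needs a limit on how much worse the new treatment may be, and a result that rules out anything beyond that limit. A test of no difference does neither. Failing to reject its null shows only that the data did not separate the arms, which a modest trial can produce when one arm is materially worse.

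As written, the only outcome that would answer the Discussion's question favourably is acupuncture being significantly better. If P exceeds 0.05, the question as worded invites the answer that acupuncture is as good as flunarizine, and the planned analysis could not support that. What is at stake is the conclusion the trial may draw from a null result. The validity of the test itself is not in doubt.

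**Working it through.** **Inputs from the document (Participants):** control responders 65%, acupuncture responders 90%, two-sided α = 0.05, power 0.9, 56 per group required, 70 per group enrolled.

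**Assumptions, not in the document:** true acupuncture rates of 55%, 50% and 65%, and non-inferiority margins of 15 and 20 points. They serve only as illustration.

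**Step 1. Reproduce the plan's sample size.** Two proportions, pooled variance under the null, no continuity correction, mean proportion (0.65 + 0.90)/2 = 0.775:

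n = [1.960 × √(2 × 0.775 × 0.225) + 1.282 × √(0.65 × 0.35 + 0.90 × 0.10)]² / 0.25² ≈ 56.5

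This is 57 when rounded up, against the stated 56. Power at 56 is 89.7%. The increase to 70 corresponds to 20% dropout (56/0.80 = 70). The stated figure is therefore an ordinary two-sided calculation for a difference, consistent with the null and the test.

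**Step 2. How often the planned test is non-significant.** Exact binomial sums, uncorrected chi-square at two-sided 5%, control rate 65%:

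| True acupuncture rate | Source of rate | P > 0.05, 70 per arm | P > 0.05, 56 per arm |
|---|---|---|---|
| 90% | plan | 4.1% | 8.9% |
| 55% (10 points worse) | assumed | 77.7% | 81.6% |
| 50% (15 points worse) | assumed | 56.5% | 64.9% |

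**Step 3. Precision if the arms are truly equal at 65% (assumed).** Standard error of the difference = √(2 × 0.65 × 0.35 / n).

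- n = 70: SE = 0.0806; 95% half-width = 1.96 × 0.0806 = 0.158, or 15.8 points.
- n = 56: SE = 0.0901; half-width = 0.177, or 17.7 points.

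**Step 4. Ability to exclude a deficit at equal rates, 70 per arm.** Power = Φ(margin/SE − 1.96), which is one-sided 2.5%.

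- 15-point margin (assumed): Φ(0.15/0.0806 − 1.96) = 46%.
- 20-point margin (assumed): Φ(0.20/0.0806 − 1.96) = 70%.

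Steps 2 to 4 show that a non-significant result from this trial would be compatible with acupuncture being clearly worse, and that the trial is not sized to demonstrate similarity when the arms are equal.

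**The case against.** The strongest reply is that the operative plan is coherent. Null, test and sample size all belong to a test of difference, and the sample size reproduces to within one patient. The aim is worded neutrally everywhere else, and the article never uses the terms equivalence or non-inferiority. Only one Discussion sentence is out of line, and it may be loose phrasing. This stands, and it is why nothing in the test or sample size needs changing. It does not remove the conflict, because the sentence is presented as the trial's question and the neutral statements elsewhere do not settle which reading governs.

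A second reply is that the harm needs both a non-significant result and a wrong reading of it. Under the plan's own rates the first is uncommon (Step 2), and a significant result in favour of acupuncture would also answer the question as worded. This stands too, and it limits the weight of the point. The protection depends, however, on a true gain near the assumed 25 points.

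A third reply is that reporting a confidence interval is often left to the full protocol or analysis plan. That is fair. The interval belongs to the remedy here, and its absence is not the fault being raised. The fault is that two statements in the same document do not fit together.

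A reader might go further and infer that the plan intends to declare equal efficacy when P > 0.05, or that this is an undersized non-inferiority trial. The document supports neither. It gives no rule for interpreting a null result, and its sample size was set for a difference. The margins in Step 4 are not the trial's own.

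**Conclusion.** The mismatch is real and can be read directly from the text: the stated question concerns equal effectiveness, while the hypothesis, test and sample size concern a difference, with no margin. A non-significant result cannot answer the stated question and could be misread as equal efficacy. Whether it would be misread cannot be told from the document.

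The mismatch matters only if the result is non-significant, and the figures for acupuncture being equal or worse rest on the assumed rates and margins. It should be corrected, but it is one sentence set against an otherwise consistent superiority design and does not reach the level of a must-fix.

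**What to change.** - Reword the question in the Discussion as one of superiority, for example whether acupuncture achieves a higher responder proportion than flunarizine, so that it matches the Participants and Statistical analysis sections.
- Report the difference in responder proportions with its 95% confidence interval.
- State that P > 0.05 will not be reported as showing that acupuncture is as effective as flunarizine.

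The sample size, null hypothesis and test stay as they are. No extra patients and no change in conduct are needed; the cost is a few sentences and one interval. The downside is that the trial gives up any claim of equal efficacy from a null result, a claim the design could not support.
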